# Study OBJECTIVES and Design (Zielsetzung der Studie)

## 3.1 Primary Hypothesis and objective

(H_p,1_) Primary hypothesis: no statistically significant difference between MWT- and DS-MWT-latencies (primary outcome measure).

(O_p_) Primary objective: We will determine whether or not – and if yes, to which extent – there is a statistically significant difference between MWT- and DS-MWT-latencies

The primary hypothesis will be tested solely on determined mean latencies and separately from additional, secondary and exploratory analyzes.

(H_s_) Additional, secondary, exploratory hypotheses: There are statistically significant correlations between conditions CPAP-withdrawal vs. CPAP-treatment to secondary test- and performance parameters (see 3.2 secondary outcome measures, see 5.2 Feature Description)

Additional, secondary, exploratory objectives are:

- (O_s-1_) We will explore, whether or not – and if yes, which and to which extent – the **test-sequence** affects MWT- and DS-MWT-latencies and other test- and performance parameters.
- (O_s-2_) We will explore, whether or not – and if yes, which and to which extent – **driving parameters** such as, for example, standard deviation of lateral position, speed, distance and steering wheel angle, SDLP, SDS, SDD and SDSW or integrated driving scores, IDS, correlate to the prior treatment or withdrawal of CPAP and the outcomes of the Epworth Sleepiness Scale (ESS) and Karolinska Sleepiness Scale (KSS) (1). Additionally, time-course-effects of, for example, SDLP will be analyzed using either repeated measures-ANOVA of 10 4-min-long modules comprising the test drive or using paired t-tests of the first and last driven module (1).
- (O_s-3_) We will explore, whether or not – and if yes, which and to which extent – **eye tracking parameters** such as, for example, blink rate, blink duration, eye openness, gaze direction, gaze duration and areas of interests (5, 6), correlate to the prior treatment or withdrawal of CPAP in the driving simulation.
- (O_s-4_) We will explore, whether or not – and if yes, which and to which extent – **EEG-features** that potentially indicate sleepiness, such as, for example, microsleep-like episodes, MSE, or individual signatures of MSE and the sleep/wake transition (7), correlate to the prior treatment or withdrawal of CPAP and the outcomes of the ESS and KSS.
- (O_s-5_) We will explore, whether or not – and if yes, which and to which extent – **repeated @home-PSG-measurements** reveal night-to-night variability of OSA-parameters (8) such as, for example, AHI, ODI, ¢SpO2, t<90, and how they correlate to other outcome parameters. CPAP data will be used to control for the adherence to the instructions and for OSA--activation control.
- (O_s-6_) We will explore, whether or not – and if yes, which and to which extent – previously identified potential (proteomic) **biomarkers for sleepiness (9-11) in non-invasive samples** such as saliva, exhaled breath, dried bloodspots (12), correlate to the prior treatment or withdrawal of CPAP and the outcomes of the ESS and KSS.

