## 3.2 Primary and secondary endpoints (outcomes, outcome measures, Zielgrössen)

Endpoints are understood as significant changes in outcome measures (see 5.2 for Feature Description for further details)

(Ep) Primary endpoint: significant difference between mean MWT- and DS-MWT-latencies.

Additional, secondary, exploratory endpoints are

(Es-1) significant differences in driving parameters

(Es-2) significant differences in ET- and EEG-features

(Es-3) significant differences in @home-PSG-recordings and test sequence

(Es-4) significant correlation to biomarkers for sleepiness in saliva and/or exhaled breath

See 5.1.2 for statistical analysis plan

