### 5.1.1 Sample size calculation

The total sample size is N_total_ = 54, consisting of the intervention group N_I_ = 36 and a healthy comparison group N_H_ = 18. (see Figure 2)

Sample sizes N_I_ = 36 for the intervention group were estimated according to formula I considering the randomized crossover RCT study design of a cohort of OSA-patients randomized both to CPAP starting condition and measurement sequence resulting in 4 groups 4 (W-DM, W-MD, C-DM, C-MD, see Figure 2) in two phases and a mixed-model ANOVA analysis. Mixed-model ANOVA accounts for the fact that repeated measures form the same person are correlated, is able to handle any missing values more effectively and considers both fixes and random effects.

[figure not shown]

Formula I

adapted from (13)

- n = Required number of participants per group.
- Z_1−α/2_​ = Z-value corresponding to the chosen significance level (e.g., 1.645 for α = 0.1 two-sided) (14).
- Z_1−β_ = Z-value corresponding to the desired power, 1.28 for 90% power) (14).
- σ = Standard deviation of the measurements = 13.5 minutes (from Bonnet & Arand) (15)
- ρ = Intra-class correlation (ICC) or correlation between repeated measures within the same participant.
- Δ = Equivalence margin or effect size = 1 pooled SD = 13.5 minutes (from Bonnet & Arand) (15)

For the sample size calculations, we use a two-sided α = 0.1 assuming that a potential difference between M and D would have a clear direction and a maximal value (bounded test range) of 40 min for the test latency. When conducting an equivalence test, using a 0.1 two-sided alpha-level effectively matches the 0.05 significance level for each side of the distribution (one for each tail), aligning the rigor of the test with the traditional hypothesis test for no difference. This assumption holds, as the reference standard deviation of 13.5 min was obtained with an equivalently bounded test range. We employ a graphically extracted and pooled standard deviation form Bonnet & Arand (15) (Figure 2 baseline and wake, p 388), the only close-to test-retest data on MWTs available.

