### 5.1.2 Statistical analysis plan

The primary hypothesis will be tested solely on determined mean latencies and separately from additional, secondary and exploratory analyzes. For the primary hypothesis, we will employ a mixed model ANOVA or generalized linear mixed model. All analyzes will be considered significant when p<0.05.

All secondary variables will be analyzed post-hoc for hypothesis-generation rather than formal testing. Collected secondary parameters will be analyzed *post hoc* individually with respect to the experimental condition (D/M) and the participants state (CPAP-treatment or withdrawal). If group-level differences exist we will conduct multiple comparison tests. Time-course-effects of, for example, SDLP are intended to be analyzed using repeated measures-ANOVA between 10 4-min-long modules comprising the test drive or using paired t-tests of the first and last driven module. Integrated Driving Scores (IDS, Z-scores) will be calculated after logistic regression of driving parameters.

For secondary parameter-based models, we will first use linear mixed models and stepwise testing will be based on biological/plausibility justification rather than purely statistical significance.

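### The trial is sized for equivalence, but its primary hypothesis, endpoint and analysis are a p<0.05 difference test with no margin in the decision rule

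*Protocol*

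**What the plan says.** Four places in the Protocol fix the primary comparison between the standard test (MWT) and the simulator test (DS-MWT).

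- Section 3.1 (hypothesis): "Primary hypothesis: no statistically significant difference between MWT- and DS-MWT-latencies (primary outcome measure".
- Section 3.2 (endpoint): "Primary endpoint: significant difference between mean MWT- and DS-MWT-latencies".
- Section 5.1.2 (analysis): "For the primary hypothesis, we will employ a mixed model ANOVA or generalized linear mixed model", followed by "All analyzes will be considered significant when p<0.05".
- Section 5.1.1 (sample size): "For the sample size calculations, we use a two-sided α = 0.1", with the reason that "When conducting an equivalence test, using a 0.1 two-sided alpha-level effectively matches the 0.05 significance level for each side". The same section sets Δ at 13.5 min, one pooled SD, and labels it as either an equivalence margin or an effect size.

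The synopsis repeats the hypothesis, the endpoint and the p<0.05 rule. The title announces a validation of the new test against the standard one. Section 2 gives as the open question whether the latencies from the two conditions are comparable.

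**The concern.** The sample size belongs to an equivalence test. The hypothesis, endpoint and analysis belong to a difference test, and no margin, confidence-interval rule or pair of one-sided tests appears in any of them. The hypothesis is that the difference test will fail to reach significance.

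That outcome depends on the standard error as much as on the difference. A precise trial with a difference well inside 13.5 min contradicts the hypothesis. An imprecise trial tends to confirm it. Neither result answers whether the two latencies agree closely enough for the tests to be treated as comparable.

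The hypothesis, endpoint and threshold are already fixed in the protocol, so a later analysis plan that used an equivalence test would contradict them.

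**Working it through.** **1. Inputs.** From section 5.1.1: SD σ = 13.5 min, Δ = 13.5 min, z = 1.645 (two-sided 0.10), z = 1.28 (90% power), four groups, 36 OSA patients. From section 5.1.2: p<0.05. The within-person correlation ρ is named in 5.1.1 but given no value, so I assume 0.5 and show 0.3 to 0.8. Each patient takes both tests in each CPAP phase, so I show one or two DS-MWT–MWT pairs per patient.

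**2. The plan's own figure.** Formula I is an image that is not available, so this step is conditional. With n = 2(1.645 + 1.28)²σ²(1 − ρ)/Δ² per group and ρ = 0.5, n = 2 × 8.556 × 0.5 = 8.56, so 9 per group and 4 × 9 = 36. ρ = 0.3 gives 48 and ρ = 0.6 gives 28. A form without the factor 2 gives 36 at ρ = 0. The value 0.5 is therefore consistent with 36 but not established by it.

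**3. Smallest observed difference that contradicts the hypothesis at N = 36.** Paired model: SE = 13.5 × √(2(1 − ρ)/pairs)/√N, with t(0.975; 35 df) = 2.030.

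| ρ | pairs | SE (min) | smallest significant difference (min) |
|---|---|---|---|
| 0.3 | 1 | 2.66 | 5.4 |
| 0.3 | 2 | 1.88 | 3.8 |
| 0.5 | 1 | 2.25 | 4.6 |
| 0.5 | 2 | 1.59 | 3.2 |
| 0.8 | 1 | 1.42 | 2.9 |
| 0.8 | 2 | 1.01 | 2.0 |

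Against 13.5 min: 2.04/13.5 = 15% and 5.40/13.5 = 40%.

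**4. Behaviour as data shrink.** True difference 5 min, ρ = 0.5, one pair. P(p≥0.05) is from the noncentral t with N − 1 df. P(equivalence) is from 400,000 simulated trials in which the 90% interval must lie inside ±13.5 min.

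| N | P(p≥0.05): hypothesis confirmed | P(equivalence shown) |
|---|---|---|
| 36 | 42% | 98% |
| 18 | 68% | 82% |
| 10 | 82% | 57% |

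The two rules move in opposite directions. The level depends on ρ and the pairs: at N = 36, P(p≥0.05) runs from 0.2% (ρ = 0.8, two pairs) to 55% (ρ = 0.3, one pair). The rise as N falls holds at every value tried.

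**5. The two rules in conflict.** Same true 5 min, N = 36, ρ = 0.5: 56% (one pair) to 86% (two pairs) of trials are both significant at 0.05 and equivalent within ±13.5 min.

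**6. False confirmation at the margin.** True difference 13.5 min, ρ = 0.5: P(p≥0.05) is about 0.01% or less at N = 36. At N = 18 with one pair it is about 2%, or 8% at ρ = 0.3. At N = 10 with one pair it is 20%, or 34% at ρ = 0.3. An equivalence test allows 5% throughout.

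**7. Power of the equivalence test.** At ±13.5 min, zero true difference, ρ = 0.5 and 36 paired completers, power exceeds 99%.

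**The case against.** Section 5.1.1 shows that equivalence was in mind, and its alpha is defensible. Two one-sided tests at 0.05 correspond to a two-sided 0.10, so the p<0.05 of section 5.1.2 could be read as the level of each one-sided test. That stands: a reader might infer a plain clash of alphas, but the numbers can be reconciled. What is missing is the named test and its margin.

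A reader might also infer that the written rule would readily pass a simulator test that is far off. The documents do not support this at the planned size. A true difference of 13.5 min is almost never missed with 36 completers. Missing a true difference of a few minutes is not false validation either, because it lies well inside the only margin the plan offers.

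Nor does any section say in words that a non-significant result establishes validity. That is an inference from the title and the hypothesis. The objective in 3.1 also asks how large any difference is, so some estimation is intended, but nothing ties the estimate to a conclusion of comparability.

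On recruitment, section 5.1.2 allows ending short of 54 but also mentions extending the study, and section 5.3 provides for replacing drop-outs. N = 18 and N = 10 above illustrate direction and are not forecasts.

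**Conclusion.** The point holds as an internal contradiction with a consequence for the primary conclusion. Section 5.1.1 plans an equivalence test, while 3.1, 3.2, 5.1.2 and the synopsis specify a difference test whose non-significance is the hypothesis. The written rule cannot support a claim of comparable latencies.

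At the planned size the demonstrable harm is mainly in one direction: an observed difference of about 3.2 to 4.6 min at ρ = 0.5 (2.0 to 5.4 min across ρ 0.8 to 0.3) would contradict comparability. False confirmation of a difference as large as 13.5 min becomes a concern only with severe under-recruitment or a narrower margin.

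These sizes rest on the plan's SD, the assumed ρ, one or two pairs per patient and a simple paired model standing in for the mixed model. I call a difference small only relative to the plan's own 13.5 min, which is about a third of the 40-min test range (13.5/40 = 34%) and itself needs justification.

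**What to change.** Rewrite the primary hypothesis (3.1), the primary endpoint (3.2), the primary analysis (5.1.2) and the matching synopsis entries as one equivalence test:

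- Estimate DS-MWT minus MWT mean latency from the mixed model in the OSA group.
- State the margin in the decision rule, labelled only as an equivalence margin, with a justification.
- Conclude equivalence only if the two-sided 90% confidence interval (two one-sided tests at 5%) lies wholly inside the margin. Otherwise conclude that equivalence was not shown.
- Report the estimate with its 95% confidence interval.
- Say that p<0.05, where it is kept for the primary, is the level of each one-sided test. State the value of ρ used in 5.1.1.

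The cost is protocol wording. At ±13.5 min and ρ = 0.5 no patients need to be added. If the margin is narrowed, the power and, if necessary, the sample size must be recalculated.

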# STUDY SYNOPSIS

| **Sponsor / Sponsor-Investigator** | Dr. rer. nat. [name]  University of Zurich (UZH),  Institute for Forensic Medicine  Division of Traffic Medicine  [name]  [name]  Switzerland  [contact]  Office: [contact]  E-Mail: [[contact]](mailto:[contact]) |
| --- | --- |
| **Study Title** | DS-MWT2 – Validating a novel driving simulation-based MWT against the standard MWT in an OSAS-cohort challenged by CPAP-withdrawal – a monocentric, controlled, randomized, crossover trial |
| **Short Title / Study ID** | DS-MWT2 |
| **Protocol Version and Date** | Version 1.1 (dated 14/02/2025) |
| **Study Registration** | SNCTP000006301, clinicaltrails.gov intended |
| **Study Category and Rationale** | Other Clinical Trial, Risk category A |

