## 5.2 Feature description

*Test-Latency:*

Mean MWT- or DS-MWT-latencies are determined by averaging latencies from four max. 40 min test- sessions determined by AASM-criteria (REF,) and previously reported additional/complementary parameters (e.g., sleep accidents with closed eyes, (1)) for the two tests, respectively.

*Driving Parameters*

We will collect multiple driving parameters, such as the standard deviation of lane position, SDLP, the standard deviation of velocity, SDS, number of lane departures, and LD. Collected parameters will also be used as one criterion to determine the sleep-accident-derived latency for the DS-MWT. IDS

*ET Features*

A recent review showed that eye movement features and the sleep-wake predictor model could be used to predict sleepiness (6). For example, the blink rate increases with increased sleep pressure and can be used to assess drowsiness or sleepiness. Other valuable ET metrics (5) for our setting are the saccade latency, saccade peak velocity and smooth pursuit velocity gain, which could also reflect levels of sleep deprivation and extreme sleepiness.

*EEG Features*

EEG recordings are required to determine MWT-latencies, based on precise identification of sleep onset (SO). According to AASM classification, sleep onset is defined as the start of the first epoch scored as any stage other than stage W. In most individuals this will usually be the first epoch of stage N1, characterized by SEM (slow eye movements) and LAMF (low-amplitude, mixed-frequency) in EEG activity. Electrophysiological data collected during both classical MWT and DS-MWT will provide useful additional insights into the sleep-wake transition. For example, microsleep episodes (MSEs), i.e., brief periods of sleep intrusion during wakefulness, may occur even before sleep onset. We will analyze manually- and automatically-detected MSEs (17).

*PSG Features*

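### The trial is titled a validation of the DS-MWT against the MWT, but it plans only a comparison of mean latency; no objective or endpoint estimates within-person agreement

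*Protocol*

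**What the plan says.** The study title in the Synopsis is "Validating a novel driving simulation-based MWT against the standard MWT in an OSAS-cohort challenged by CPAP-withdrawal". Section 2 gives the evidence gap as whether latencies from the two tests can be compared and whether they reflect clinical features of sleepiness. It envisages the simulator test as a possible complement to the MWT that could help to find sleepy people before they drive.

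Section 3.1 says of the primary hypothesis: "The primary hypothesis will be tested solely on determined mean latencies and separately from additional, secondary and exploratory analyzes". A participant's latency on each test is "determined by averaging latencies from four max. 40 min test- sessions" (section 5.2). Section 3.2 then sets the "Primary endpoint: significant difference between mean MWT- and DS-MWT-latencies". Section 5.1.2 adds: "For the primary hypothesis, we will employ a mixed model ANOVA or generalized linear mixed model" and "All analyzes will be considered significant when p<0.05".

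The secondary objectives and endpoints cover test sequence, driving parameters, eye tracking, EEG, home PSG and biomarkers. The run-level and module-level models in 5.1.2 predict sleep onset or sleep accidents. Correlation within a participant appears only in the list of terms for Formula I in 5.1.1, as "ρ = Intra-class correlation (ICC) or correlation between repeated measures within the same participant", and no value is given.

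**The concern.** Two tests can have the same average latency in a group while ranking or classifying the same people differently. A paired or mixed-model analysis uses the within-person correlation to sharpen the estimate of the mean difference. It does not report how far one driver's two results lie apart. For a test meant to help identify sleepy individuals, that distance is what a user needs to know.

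The design already yields the data. By section 4.3, visits 3 and 4 fall on consecutive days, as do visits 6 and 7, and each pair of visits holds one test of each kind in one CPAP state. As the objectives stand, a non-significant mean difference could be reported under a title that promises validation, with nothing planned to show whether individual results agree.

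**Working it through.** **Inputs**
- OSA planning SD σ = 13.5 min and margin or effect size Δ = 13.5 min (5.1.1).
- z = 1.645 for two-sided α = 0.1, and z = 1.28 for 90% power (5.1.1).
- Four groups, 36 OSA patients (5.1.1).
- Healthy SD 5.9 min (5.1.1). Latency bounded at 40 min (5.1.1).
- ρ: no value in the protocol. It is an assumption here, shown as a range.

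**1. The plan's own figure.** The image of Formula I is not shown. A form that uses the listed terms is n per group = 2(z₁ + z₂)²σ²(1 − ρ)/Δ². With σ = Δ and ρ = 0.5 it gives 2 × (1.645 + 1.28)² × 0.5 = 8.56, so 9 per group and 4 × 9 = 36. A form without ρ, (z₁ + z₂)²σ²/Δ² = 8.56, also gives 36. So ρ = 0.5 is compatible with the sample size but is not established by it.

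**2. Spread of one driver's difference.** SD_d = σ√(2(1 − ρ)), and the 95% limits of agreement around a mean difference of 0 are ±1.96 × SD_d.

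| ρ (assumed) | SD_d, OSA (min) | 95% limits, OSA (min) |
| --- | --- | --- |
| 0.2 | 17.1 | ±33.5 |
| 0.5 | 13.5 | ±26.5 |
| 0.7 | 10.5 | ±20.5 |
| 0.8 | 8.5 | ±16.7 |

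The limits equal ±20 min at ρ = 1 − ½ × (20/(1.96 × 13.5))² = 0.714, so they exceed 20 min only below about 0.71. Under a normal distribution the share of OSA drivers whose two results differ by more than 20 min is about 14% at ρ = 0.5 (about 5 of 36), 5.6% at 0.7 and 1.9% at 0.8.

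**3. Healthy group.** At ρ = 0 the limits are 1.96 × 5.9 × √2 = ±16.4 min, and they narrow as ρ rises. They stay below 20 min at any ρ ≥ 0.

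**4. What the planned test sees.** With 36 pairs and ρ = 0.5 the SE of the mean difference is 13.5/√36 = 2.25 min. If the true mean difference is 0, a test at p<0.05 is non-significant in 95% of trials by construction. Simulation of 36 pairs at ρ of 0, 0.3, 0.5, 0.7 and 0.8 gave 95% each time. A 13.5 min equivalence test on the mean, at ρ = 0.5, passed in over 99.9%. Neither result depends on the individual differences being small.

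**5. Normal approximation.** An SD of 13.5 min on a 0–40 min scale is larger than that of a uniform distribution (40/√12 = 11.5 min), so the limits above are rough. A simulation with latencies confined to 0–40 min, means of 20 to 30 min and a copula correlation of 0.5 put 17–20% of drivers beyond 20 min. The achieved correlations there were 0.41–0.47, which explains part of the increase over 14%.

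**The case against.** The protocol is more modest than its title. It says that the simulator test might complement the MWT, calls the study small and exploratory, and warns that the results may not generalise. It nowhere claims that the tests are interchangeable. A reader might infer that deciding one person's fitness to drive is the stated use; the text supports only an envisaged use. That stands, and it limits how strongly the point can be put. It does not remove the mismatch between a validation title and a comparison of means.

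A reader might also take the sentence quoted from 3.1 as proof that only group means are compared. In that sentence the mean is each participant's average over four runs. The group-level comparison follows from the endpoint in 3.2 and the model in 5.1.2.

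A third tempting inference is that the tests will disagree by more than 20 min. The documents do not support it: ρ is unstated, the SD was read from a figure in a published study and pooled over two conditions, and the calculation applies to OSA patients only.

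Finally, a separate SAP could add an agreement analysis. But objectives and endpoints are fixed in the protocol, and agreement is not among them.

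**Conclusion.** The point holds in a limited form. The only planned comparison of the two tests is a difference in mean latency, and nothing in 3.1, 3.2 or 5.1.2 estimates within-person agreement. The protocol's own planning SD leaves room for large individual differences in OSA patients, but how large depends on the assumed correlation and on rough normal theory. The healthy group does not show the problem on the same scale.

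It would go too far to say that the planned analysis always returns no difference: with a true difference of 0, about 5% of trials would still reject. It would also go too far to read a non-significant result as equivalence of the means, because the stated analysis is a difference test at p<0.05. The change should be made, since it lets the trial answer the question in its title from data that it already collects.

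**What to change.** Add to 3.2 and 5.1.2 a named secondary endpoint: within-person agreement between DS-MWT and MWT mean latency. Report the bias and 95% limits of agreement from the mixed model, by CPAP state, together with an ICC or concordance coefficient, all with confidence intervals. Fix in advance the limit of disagreement that would be acceptable, with its reason.

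Restrict the primary conclusion to the difference in mean latency with its CI. Use the word equivalence only if the primary analysis becomes an equivalence test against a stated margin. Base any claim of validity for individual use on the agreement results.

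The cost is one more analysis on data already planned, with no extra visits or patients, and a conclusion that may be less favourable. Two limits should be stated:
- **Precision.** With 36 pairs and ρ = 0.5, each limit has a standard error of about 13.5 × √(3/36) = 3.9 min, so its 95% CI is about ±8 min (3.9 × 2.03 = 7.9).
- **Interpretation.** Neither test is repeated within a CPAP state, so the limits combine disagreement between the tests with day-to-day variation in the patient.
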